## Abstract

**Background:**

A consistently demonstrated overlap exists between the occurrence of domestic violence and child maltreatment, yet these issues are historically addressed by distinct systems and programming. The randomized control trial pilot study presented in this article adapts, implements, and tests a new approach for addressing family violence for Latinx families with co-occurring risk for domestic violence and child maltreatment. In doing so, this pilot study addresses the clear need for collaboration between the two fields and focuses on Latinx families, who often face specific challenges regarding seeking and receiving needed services. The primary aim of the current study is a pilot implementation of SafeCare+®, an evidence-based parenting curriculum (SafeCare®) augmented with a healthy relationships curriculum (SafeCare+®). The objectives are a reduction of family violence, improved communication, and a healthy home environment for children in Latinx families with co-occurring domestic violence and child maltreatment.

**Methods:**

This protocol outlines a feasibility, randomized control trial to examine the potential efficacy of SafeCare+. The pilot study is divided into two phases. Components of phase one involve developing a detailed implementation and evaluation plan, including a community needs assessment, determining screening and outcome measures, and assuring all components are culturally appropriate for the target population. Phase two implements the randomization of parents, who are involved in the child welfare system and referred for in-home parenting services, into SafeCare+ or SafeCare as usual. Participants complete assessments regarding mental health, provider-parent relationship, interpersonal violence experiences, and fidelity to the intervention. Analyses will focus on improvement on target outcomes for the intervention group, as well as comparison to the control group.

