### Design

The pilot study is divided into two phases. During phase one, the first year of the study, community and academic partners collaborate to develop a detailed evaluation plan. The evaluation centers on the effective implementation of SC+ and measurement of relevant outcomes during phase two of the project—the RCT, pilot study. Components of phase one include (1) a community needs assessment, (2) refining the target population, (3) designing the evaluation plan, (4) determining screening and outcome measures, (5) conducting focus groups with key stakeholders, including DV providers and Latinx survivors, to assure that the chosen interventions and screening and assessment tools are culturally appropriate for the target population, and (6) ensuring the proper training of direct service staff. For phase two, the RCT pilot study will enroll at least 160 parents either into SC or SC+, allocating a minimum of 80 parents per condition. Parents will be randomized to SC or SC+ and within home visitor, such that every other eligible parent will be assigned to SC or SC+ within home visitor. The nested structure will be accounted for in multi-level analyses, see Fig. 1 (SafeCare+ study flow diagram).

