### Feasibility outcomes

Acceptability of the intervention will be examined in both phases of the study. First, focus groups with the target population participants will determine the perceived fit of the intervention for the population. Focus groups will also provide information regarding the variety of experiences, barriers, and strengths that exist within various sub-groups of the target population (e.g., younger and older parents, recent immigrants). This information will be used to design and test various approaches to service delivery to meet the varied needs of the target population and to determine the feasibility for expanding the target population to include a prevention base for families at risk of DV. Second, satisfaction will be established by program participants on all intervention components. In addition to acceptability, SC+ limited effectiveness will be ascertained by comparisons between the experimental and control groups on key outcome measures, set to achieve at minimally medium effect size. Finally, practicality (i.e., perceived sustainability within the existing infrastructure) will be explored at the conclusion of the study via interviews with providers and service system leadership.

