#### Screening measures

*Hurt*, *Insult*, *Threaten*, *Scream* (HITS) [30] is a 4-item instrument for DV screening. Items ask respondents how often their partner physically hurt, insulted, threatened with harm, and screamed at them. A score of 10.5 (range 4 to 20) was demonstrated to reliably differentiate victims of domestic abuse from family practice patients. The current pilot study includes parents who report a score of 7 or higher.

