#### Outcome measures

*SC+ model fidelity* is assessed via client report, with clients completing a fidelity questionnaire at the end of every SC or SC+ session. The fidelity survey was adapted from the National SafeCare Training and Research Center training checklists, and the fidelity measure has been validated over the course of SC implementation [31]. Overall, monitoring of fidelity allows for measuring the effectiveness of the intervention as designed, as well as any practice changes which are naturally occurring and may need to be addressed.

*The Conflict Tactics Scales* (CTS2)*-short form* [32, 33] measures both the extent to which partners in a dating, cohabiting, or marital relationship engage in psychological and physical attacks on each other, as well as use of reasoning or negotiation to deal with conflicts. Participants are asked about the frequency of concrete acts and events within the past 6 months for their baseline CTS2 assessment, with the time frame changed to assessing if these acts and events occur within the past 2 months for the post-intervention assessment.

*The Center for Epidemiological Studies Depression Scale* (CES-D) [34] is a 20-item questionnaire, which assesses depressive symptomology. Designed as a short self-report tool, each item asks about the last week and is responded to using a 4-point format. The CES-D has high internal consistency and adequate test-retest repeatability.

*Relationship self-efficacy* (RSE) [35] is a 35-item measure evaluating relationship maintenance self-efficacy beliefs. Thirteen items relevant to the content of HR are included, across the three domains of emotional control, differentiation, and mutuality. Emotional control denotes the ability to appropriately regulate negative feelings with others. Differentiation is the capacity to assert clear interpersonal boundaries and express the need for separateness. Mutuality is defined as being able to provide care and receive support.

*Working Alliance Inventory* (WAI) [36] assesses working alliance between parents and their service providers. The current study employs the short-form, 12-item version of the WAI [37] and includes the components of goal, task, and bond. Goal is the extent to which the client and provider agree on goals of services. Task is the degree to which the client and provider agree on ways of achieving stated goals. Bond denotes mutual liking between client and provider.

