#### Sample size

A conservative estimate for the duration of the proposed study is 160 parents, which provides an adequate sample size required to discern improvement, with a medium Cohen’s *d* effect size, on the proposed measures.

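### The abstract makes improvement within the SC+ arm a focus of analysis, but pre-post change there cannot isolate the HR module; conclusions should rest on the between-arm contrast

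*Protocol article*

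**What the plan says.** The Methods paragraph of the abstract gives the analysis two targets: "Analyses will focus on improvement on target outcomes for the intervention group, as well as comparison to the control group". The Feasibility outcomes section gives one: "SC+ limited effectiveness will be ascertained by comparisons between the experimental and control groups on key outcome measures, set to achieve at minimally medium effect".

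The Data analyses section plans mixed models with change in CTS2, depression, relationship self-efficacy and fidelity as dependent variables. It does not say which model coefficient carries the conclusion about SC+. The Sample size section calls 160 parents a number "which provides an adequate sample size required to discern improvement, with a medium Cohen’s *d* effect size, on the proposed measures", without naming the contrast. The Design section adds that "the RCT pilot study will enroll at least 160 parents either into SC or SC+, allocating a minimum of 80 parents per condition".

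Three features bear on how change within the SC+ arm can be read:

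- SC+ is SafeCare with the HR module added, and eligibility requires that parents already receive SafeCare.
- The CTS2 asks about the past 6 months at baseline, "with the time frame changed to assessing if these acts and events occur within the past 2 months for the post-intervention assessment". No rescaling is stated. The CES-D window does not change: "each item asks about the last week and is responded to using a 4-point format".
- Entry depends on the HITS screen: "The current pilot study includes parents who report a score of 7 or higher".

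**The concern.** The Discussion section names the effectiveness of the HR curriculum as a primary aim, and the abstract says the findings will inform whether to proceed to a definitive trial. If SC+ parents improve and SC parents improve by the same amount, the abstract's first focus is met while the criterion under Feasibility outcomes is not. The article does not say which would prevail.

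This matters because change within SC+ contains more than any HR effect. It includes whatever SafeCare does, any drift after selection on a screening score and, for the CTS2, the effect of asking about a shorter period. The CTS2 is the outcome most exposed, and the Data analyses section lists it first.

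**Working it through.** **1. The plan's own figure.** Alpha, power and a numerical d are not stated, so 160 cannot be reproduced exactly. I assume d = 0.5 and two-sided alpha 0.05.

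- Between arms: n per arm = 2(z₀.₉₇₅ + z_power)²/d². At 80% power this is 2(1.960 + 0.842)²/0.25, or 63 per arm (126 in all). At 90% power it is 85 per arm (170).
- Power with 80 per arm: Φ(0.5·√(80/2) − 1.960) = Φ(1.202) = 88.5%, before clustering and attrition.
- Within one arm, paired, 80% power: n = 2(1 − ρ)(2.802/0.5)², which gives 44, 32 and 19 parents at pre-post correlation ρ = 0.3, 0.5 and 0.7.

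So 80 per arm fits a between-arm medium effect and far exceeds what a within-arm test would need.

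**2. CTS2 recall window, no HR effect.** At a constant monthly rate λ, the expected count goes from 6λ to 2λ, a fall of 4λ/6λ = two thirds. To express this in SDs, let rates vary between parents as a gamma distribution with shape k (assumed). The baseline SD is then √(6λ + 36λ²/k), and the apparent improvement is 4λ/√(6λ + 36λ²/k).

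- λ = 0.1, k = 0.5: 0.4/√1.32 = 0.35.
- λ = 1.0, k = 1.0: 4/√42 = 0.62.

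Eight settings were simulated (λ = 0.1, 0.25, 0.5, 1.0; k = 0.5, 1.0), with 4000 trials each, 80 parents per arm, and t-tests on raw change that ignore clustering. Four of them:

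| λ | k | Fall, baseline SD | Any act, 6 → 2 months | Within SC+ significant | SC+ vs SC significant |
|---|---|---|---|---|---|
| 0.1 | 0.5 | 0.35 | 33% → 16% | 97% | 5% |
| 0.25 | 1.0 | 0.52 | 60% → 33% | 100% | 5% |
| 1.0 | 0.5 | 0.45 | 72% → 55% | 100% | 5% |
| 1.0 | 1.0 | 0.62 | 86% → 67% | 100% | 4% |

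Over all eight settings the fall is 0.35 to 0.62 SD. The within-arm test is significant in 97% to 100% of trials and the between-arm test in 4% to 6%.

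**3. Regression to the mean after HITS selection.** Under normality the expected fall is (r₀ − r₁) × φ(c)/p. Here r₀ and r₁ are the correlations of HITS with the baseline and later outcome, p is the fraction of screened parents selected, and c is the corresponding cut. The article gives none of these. With r₀ − r₁ from 0.05 to 0.3 and p from 50% to 10%:

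- smallest: 0.05 × 0.80 = 0.04 SD;
- largest: 0.3 × 1.75 = 0.53 SD.

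These are SDs of the outcome among screened parents.

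**4. What a shared drift does to a within-arm test.** With 80 parents, SE = √(2(1 − ρ)/80) in outcome SDs, and the chance of a significant improvement is Φ(drift/SE − 1.960). For ρ from 0.3 to 0.7 and no HR effect:

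- drift 0.1 SD: 11% to 21%;
- drift 0.2 SD: 33% to 64%;
- drift 0.3 SD: 62% to 93%.

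**5. SafeCare itself.** Expected change is S + H in SC+ and S in SC, where S collects everything shared and H is the HR effect. The SC+ arm alone yields only S + H; the difference between arms yields H. The SafeCare benefits cited in the Interventions section concern child health, home safety, parent-child interaction and child-welfare recidivism. None is a client outcome listed for analysis, so the size of this part of S cannot be computed from the article.

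**The case against.** The best defence is that the body of the article already does what is asked. Feasibility outcomes rests effectiveness on the control comparison, and the control arm is measured over a matching period. Shared influences then cancel in expectation. This stands, and it limits the point: the randomised contrast is not impugned.

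Several stronger readings are tempting, and the documents do not support them:

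- *Within-arm change ranks first.* A reader might infer this from the word order of the abstract. The sentence joins two foci without ranking them, and no section specifies a within-arm test. The error rates above show what such a test would do, not what the plan commits to.
- *The trial was sized for within-arm improvement.* The phrase "adequate sample size required to discern improvement" is loose, but step 1 and the matching reference to a medium effect under Feasibility outcomes point to a between-arm aim.
- *Selection, SafeCare and the recall window all produce improvement.* Only the recall effect follows directly from the stated design, and it is confined to the CTS2. HITS runs from 4 to 20, the article cites 10.5 as the score separating victims, and entry at 7 was meant to be inclusive. Selection may therefore be mild and regression to the mean near its lower end. Nobody is selected on the CES-D or on relationship self-efficacy.
- *A favourable within-arm result will drive progression.* The article says only that findings will inform that decision.

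It is also fair to object that the two-thirds fall assumes frequency scoring without rescaling, and that a fuller plan might rescale. Scoring any act against none would change the size of the artefact but not remove it: in the simulated settings the proportion reporting any act still falls by 17 to 27 percentage points.

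What remains is that within-arm improvement is a stated focus, nothing calls it descriptive, and the article does not say which result governs.

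**Conclusion.** The point holds as an inconsistency that should be reconciled. The abstract gives improvement within SC+ standing as a focus of analysis, whereas Feasibility outcomes judges effectiveness between arms. Change within SC+ cannot show an HR effect on any outcome, because SafeCare and HR are inseparable in that arm. This needs no numerical assumption.

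For the CTS2 the consequence is large. A frequency score that is not rescaled would show an apparent improvement of about 0.35 to 0.62 baseline SD under the null, given a constant event rate and the assumed rates and spread. That is around the medium size the plan looks for. A within-arm test would almost always be significant, while the between-arm test keeps roughly its 5% level. For the other outcomes the size is unknown: regression to the mean is plausible but rests on assumed inputs, and a SafeCare effect on domestic violence, depression or relationship self-efficacy is possible but not shown. The figure of 160 is not disputed here.

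**What to change.** - In the abstract's Methods paragraph and in Data analyses, state that conclusions about SC+ and the progression decision rest on the randomised between-arm contrast (arm-by-time, or arm adjusted for baseline), and that change within an arm is descriptive only.
- In Sample size, describe the target as a between-arm difference of medium size, consistent with Feasibility outcomes.
- Where within-arm CTS2 change is still described, show the two recall windows beside it.

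This costs wording only. No new data are needed, since the control arm is already measured over a matching period. The price is that improvement within SC+ can no longer be presented as a headline result.

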**Discussion:**

This study will provide evidence on the feasibility and potential effectiveness of an early intervention program aimed at improving communication skills and mental health and reducing incidents of violence for Latinx parents who are involved with the child welfare service system. The findings of the study will inform the decision to progress to a full scale, definitive randomized control trial to test the effectiveness of an intervention, delivered as part of home visitation, for improving outcomes for families with histories of domestic violence.

**Trial registration:**

ClinicalTrials.gov, NCT03041558; registered 2 February, 2017—retrospectively registered.

## Background

Child maltreatment and domestic violence (DV) are two vital public health concerns, often with considerable overlap and in extensive need of amelioration. Over 4 million cases of suspected child maltreatment were reported to state child protective service systems in the USA in 2017, with approximately 674,000 confirmed cases of maltreatment. The most common form of child maltreatment in the USA is neglect, accounting for over 74% of substantiated cases [1]. The individual and societal impacts of child maltreatment are well documented, as child trauma is associated with negative social, emotional, behavioral, and health effects on children and youth [2] at a notable economic cost [3–5]. The impacts of DV are similarly alarming. In the USA, over 1 in 3 (or 42.6 million) women experienced violence by an intimate partner over the course of a lifetime, with 6.6 million women reporting violence within the last year [6]. Approximately 15.5 million children are exposed to DV each year, with over 50% of DV incidents occurring in households with children [7].

### Co-occurrence of domestic violence and child maltreatment

Two decades of research have clearly documented a strong overlap between DV and child maltreatment, with national research indicating a 30 to 60% co-occurrence rate [8, 9]. These forms of family violence have a strong likelihood of co-occurring because they share several common risk factors, such as young maternal age, low level of education, and low socioeconomic status, among others [10, 11]. Children who have witnessed or experienced violence in their homes face an elevated risk of cognitive and emotional problems [12]. They often experience negative outcomes such as poor school performance, grade retention, juvenile delinquency, and teenage pregnancy [8]. Further, children who reside in homes with DV may show warning signs of stress, fear, and trauma [13].

While child maltreatment clearly has an adverse effect on healthy child development, the presence of DV can also interfere with parenting, placing children at additional risk. Children living in households with DV are more likely to experience emotional, physical, and sexual abuse [14]. Perpetrators often attempt to control their adult partners through methods such as intimidation, undermining their parental authority, or using children against the other parent [15]. Children may be injured when they attempt to intervene in a DV incident or get struck by objects intended to injure or frighten the parental victim. And, in the absence of physical abuse, DV may deteriorate the family environment and increase stress, impacting parents’ capacity to attend to their children’s needs.

Taken together, there is a clear need for collaborative efforts to provide appropriate services and to identify families struggling with relationship dynamics earlier in the cycle of family violence. Despite the growing awareness of the co-occurrence of DV and child maltreatment, however, programs and systems have historically responded separately. Existing parenting programs designed to address child maltreatment rarely include training in managing DV-related issues. However, the presence of DV has been shown to affect domains of improvement that are targeted by parenting programs. For example, a common element of many parenting programs is a focus on improving parent-child interactions. DV perpetrators often damage the parent-child relationship by victim-blaming and breeding distrust in what is typically the mother’s ability to protect her children [16]. Including content that addresses DV in the context of parenting programs creates a unique opportunity to both deliver services that acknowledge the complexity of the intersection of DV and parenting and provide early intervention to children and parents at risk for long term, negative outcomes.

### Need for culturally relevant and trauma-informed services for Latinx families

In addition to addressing service needs for families with co-occurring risk for DV and child maltreatment, the current study specifically focuses on Latinx families. The characteristics or consequences of DV among different cultures may vary. Attention to cultural differences among DV survivors can attune services to particular psychological, emotional, spiritual, economic, legal, and social needs. Cultural factors unique to the Latinx community that may impact the manifestation of DV include concepts such as *machismo* or *marianismo* [17]. These gender ideals encourage men to be dominant in intimate relationships and for women to demonstrate submissive and passive behaviors [18, 19]. Some evidence demonstrates that the effects of DV on Latina women lead to significantly greater trauma-related symptoms and depression as compared to non-Latina women [20].

The Latinx community in the USA covers a wide range of experiences, from recent immigrants with limited command of the English language, to families with generations of citizenship. Latina immigrants may have difficulty recognizing or responding to DV due to patriarchal values and beliefs in *familismo*, or family loyalty [21]. Even when DV is identified as an issue, Latina survivors can often face other obstacles in seeking help. Common barriers to help-seeking behaviors include lack of English proficiency, fear of deportation, and perception that law enforcement will not respond to domestic disputes [22]. Latinx families may face a range of additional risk factors such as recent immigration, resulting in great distance from traditional support systems, challenges related to cultural expectations, religion, and previous experiences of violence [23]. These factors may elevate traumatic stress reactions, indicating a clear need for collaborative efforts that focus on (1) identifying these families earlier in the cycle of family violence, (2) supporting them to garner the necessary skills to keep themselves and their families safe and healthy, and (3) providing safety planning and violence prevention.

### In-home parenting programs as a unique platform to provide early intervention for DV

The primary aim of the current study is a pilot implementation and testing of culturally relevant, trauma-informed programming to lead to a reduction of family violence, a resulting increase in family stability, improved communication, and a healthy home environment for children in Latinx families with co-occurring DV and child maltreatment. Specific objectives include the following:
Increased access to culturally specific, trauma-informed, evidence-informed interventions.Increased understanding of the needs of the target population and how to meet them.Improved collaboration, policies, and practices for effectively meeting the needs of the target population.Reduced incidents of DV at case closure.Improved mental health at case closure.Improved communication skills at case closure.

The intervention being implemented is SafeCare+ (SC+), an evidence-based (EB) training curriculum for parents referred for child maltreatment, enhanced with the healthy relationships (HR) module. SafeCare (SC) has been shown to be widely accepted among the Latinx community [24]. The HR enhancement is a promising practice that may prevent and/or reduce family violence among Latinx families. The study will test the efficacy of the SC+ model, contributing to the DV field’s evidence base of effective practices that improve outcomes for Latinx families impacted by both DV and child maltreatment. The evaluation of the pilot implementation will impact and inform advocacy and practice change.

